### Secondary outcomes

#### Demographics and other data at cluster level

At the municipality/city district level, we will include data on the total number of home-dwelling older adults (65 years and older) and the total number of older adults receiving the following services: safety alarm service, home nursing, practical assistance, rehabilitation services, preventive services and fall prevention interventions. Additionally, we will collect data on other ongoing interventions on fall prevention, such as exercise groups for older adults with a low risk of falls, exercise groups for older adults with a medium risk of falls, assessment and interventions for older adults with a high risk of falls and systems for monitoring falls. We will also collect data on the distribution of information and education to service users and health care professionals, in addition to if and how fall prevention is included in strategic documents. If available, data on the number of falls in older adults will be collected.

#### Fall injuries

The number of fall injuries per cluster will be collected along with registered diagnosis and procedure codes capturing sprains and fractures in the Municipal Care Registry (KPR) and Norwegian patient registry (NPR).

#### Feasibility of the clinical recommendations

At an individual level, health professionals within each cluster will answer questions related to the feasibility of the clinical recommendations by use of the Feasibility of Intervention Measure (FIM), a four-item questionnaire with a five-point scale ranging from completely disagree to completely agree [49].

#### Experience of the implementation processes

We will use the Normalization Measure Development Questionnaire (NoMAD) to measure the implementation processes from the perspective of health professionals [50, 51]. This questionnaire is suited when evaluating the implementation of complex interventions in health care [52]. It is a questionnaire consisting of 20 items with a five-point scale ranging from completely agree to completely disagree.

#### Intervention costs

We will carry out an economic evaluation of the costs of the implementation intervention. During the intervention phase, we will collect data on the costs of the FALLPREVENT intervention. The data will consist of the time-use for the intervention (resource teams, seminars and meetings) and the number of health professionals participating in the meetings and seminars and their job positions and education.

### Interview with health professionals and managers

We will collect qualitative data to explore the participants’ experience of the implementation intervention. We will carry out face-to-face focus group interviews (one to two per region) with six to eight health professionals from the resource groups immediately after the end of the intervention. Topics to be discussed will include their experiences with the implementation intervention, working in an interprofessional team and applying the knowledge on implementation and fall prevention to their clinical practise. In addition, we will perform digital semi-structured interviews with ten to twelve managers from the intervention clusters to discuss their role as managers during implementation and their experiences with the implementation intervention.

### Sample size

We did a sample size calculation based on the primary outcome; health professionals’ adherence to the national recommendations, a ten-item questionnaire with answers scored according to a five-point Likert scale. The sample size calculation accounts for the intra-cluster correlation coefficient, the number of clusters, the number of responders in each cluster and the expected effect expressed as the mean difference between the intervention and the control group in relation to the standard deviation of the outcome within each group [53]. The expected effect is equal to Cohen’s *d* effect size of 0.5 (i.e., the mean difference between groups equal to 0.5 standard deviation of the outcome variable). With an assumed intra-cluster correlation of 0.1 and 12 clusters in the intervention and 12 in the control arm, we require 10 participants in each cluster to obtain 80% statistical power at a 5% significance level—totalling 120 participants in each randomised group. However, to allow for missing data, dropouts and uncertainties about the expected effect and intra-cluster correlation, we will include an average of 30 responders from each cluster.

### Statistical analysis and data management

We will explore the effectiveness of the tailored interventions to implement the national fall prevention recommendations in the municipalities. A statistician blinded to group allocation will undertake the statistical analysis. A complete data analysis plan was finalised and published on April 21, 2023, in the open science framework https://doi.org/10.17605/OSF.IO/EPG72.

The effectiveness of the intervention with the mean (95% CI) or median (IQR) adherence, will be calculated from data recorded by the adherence questionnaire. We will evaluate the change in adherence sum score from baseline to follow-up, for the intervention group compared to the control group. The main intention to treat analyses will include all the 30 responders from each randomised cluster, regardless of protocol fidelity. To provide further insight into the effectiveness of the intervention, per-protocol analyses will be carried out where we will include all participants in randomised municipalities and city districts meeting the study eligibility criteria and with no major protocol deviations affecting the treatment efficacy. To consider cluster effect and repeated measurements, generalised linear mixed model with cluster and subject-specific random intercept will be used as the main method as outlined by Twisk [53]. If the pre-specified statistical model does not converge, we will assess equivalent statistical models with a simpler structure or use generalised estimating equations or robust standard errors. Fixed effects in the model are the outcome variable at baseline as a covariate and time, intervention group and the interaction between time and intervention. It will be compared to basic methods that do not consider cluster effect, e.g., independent sample *t* test, Mann–Whitney *U* tests or chi-square tests. Missing data will be left missing; no imputation methods will be used in the primary statistical analysis.

To assess the economic costs of the intervention we will present a detailed documentation of the incurred costs. The documentation will discern which components, such as costs related to travel time and personnel commitment, are driving the cost of the intervention. To evaluate the cost of the intervention on adherence, we will compute the cost per percentage point increase in adherence sum score. We will conduct a sensitivity analysis to account for uncertainty in cost and effect estimates.

We will design questionnaires in “Nettskjema”, which is a secure data capture tool developed by the University of Oslo, that offers a range of functions to collect, store and analyse data from the desired target group. The researcher will send a link by email to the participants and then the answers are returned to the same portal. The participants will have to provide informed consent before filling out the questionnaire. Questionnaires will be stored and de-identified in OneDrive with access control and login during analysis. After the end of the study, data will be anonymised according to the approval of The Norwegian Agency for Shared Services in Education and Research (SIKT) [54]. Personally identifiable information will be removed or rewritten.

We will record all individual and focus group interviews using a digital voice recorder and transcribe them before data analysis. We will analyse the transcript using reflexive thematic analysis by Braun and Clark [49], using the six-step method to identify, analyse and report qualitative data patterns. Audio recordings will be directly uploaded to and saved in “Nettskjema”. When conducting interviews digitally through Zoom, we will store the recordings safely in Microsoft OneDrive with access control and login.

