### Data collection and randomisation

We will collect data at baseline (T0: August 2023) prior to randomisation, immediately after the end of the intervention period (T1: May 2024) and then 6 months later (T2: November 2024). Data for the study will be drawn from multiple sources. We will send three online questionnaires, including an informed consent form, to the 30 health professionals recruited from each cluster at T0, T1 and T2. The coordinators will collect the data at cluster level and report this by use of an online questionnaire at T0, T1 and T2. We will collect data on resource use for the intervention group during the intervention period, and we will draw data on injurious falls retrospectively from health registers. We will collect qualitative data from interviews with health professionals and managers in the intervention group at T1 and T2. Figure 2 presents a logic model for the FALLPREVENT intervention, summarising the proposed links between the input, activities, audience, output and outcomes.

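### The intention-to-treat set is said to be all 30 responders per cluster, but a baseline covariate with no imputation drops anyone lacking a T0 score and gives no weight to anyone lacking both follow-ups

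*Protocol article*

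**What the plan says.** Three statements in one paragraph of the protocol article (Statistical analysis and data management) bear on who is analysed:

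- The analysis set: "The main intention to treat analyses will include all the 30 responders from each randomised cluster, regardless of protocol fidelity".
- The model: a "generalised linear mixed model with cluster and subject-specific random intercept will be used as the main method", and "Fixed effects in the model are the outcome variable at baseline as a covariate", together with time, group and their interaction.
- The missing-data rule: "Missing data will be left missing; no imputation methods will be used in the primary statistical analysis".

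The scores come from separate online questionnaires, sent "to the 30 health professionals recruited from each cluster at T0, T1 and T2" (Data collection and randomisation). The Sample size section expects gaps: recruitment is raised from 10 to 30 per cluster "to allow for missing data, dropouts and uncertainties about the expected effect and intra-cluster correlation". That section also says "we will include an average of 30 responders from each cluster", and the abstract gives 30 as a maximum per cluster, so a fixed 30 does not match the article's other descriptions of cluster size.

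**The concern.** A likelihood-based mixed model copes with missing outcomes but not with missing covariates. Once T0 is on the right-hand side and may not be imputed, a record without T0 cannot enter the likelihood, whatever was observed later. A professional with T0 only has no post-baseline outcome. The three statements are compatible only if every recruit supplies T0 and at least one of T1 and T2, and the Sample size section does not expect that.

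Two things are at stake. Observed follow-up scores from people without T0 would be discarded, which costs precision. And the trial report would attach the intention-to-treat label, with a claim of full inclusion, to what is really a set with a baseline and at least one follow-up.

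**Working it through.** **The protocol's own figure.** Inputs from Sample size: d = 0.5, intra-cluster correlation 0.1, 12 clusters per arm, 10 per cluster, 80% power, 5% level (taken as two-sided).

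- Unadjusted n per arm = 2 × ((1.96 + 0.842)/0.5)² = 62.8.
- Design effect = 1 + (10 − 1) × 0.1 = 1.9.
- 62.8 × 1.9 = 119.3, so 120 per arm. This reproduces; power at 12 × 10 per arm is 80.2% (normal approximation).

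**Who enters the stated model.**

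| Scores observed | In the stated model? | With T0 as an outcome? |
|---|---|---|
| T0 and at least one of T1, T2 | Yes | Yes |
| T1 and/or T2, no T0 | No | Yes |
| T0 only | No post-baseline row | Present, but adds almost nothing to the contrast |
| None | No | No |

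**Illustration.** The article gives no missingness rates, so these are assumed: 15% at T0, 30% at T1, 40% at T2, independent. One data set of 25 × 30 = 750 was simulated.

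- No T0: 125. Neither T1 nor T2: 98. Either condition: 207. No score at all: 125 + 98 − 207 = 16.
- Used by the stated model: 750 − 207 = 543 (72%).
- The 207 split into 125 − 16 = 109 with follow-up but no T0, 98 − 16 = 82 with T0 only, and 16 with nothing.
- With T0 as an outcome: 750 − 16 = 734. The useful gain is the 109, since the 82 carry almost no information on the contrast.

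**Range.** Let a be the proportion without T0 and b the proportion without both follow-ups, independent. The share kept is (1 − a)(1 − b), and the share with follow-up but no T0 is a(1 − b).

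- a = 5%, b = 10%: kept 0.95 × 0.90 = 0.855, or 641 people (25.6 per cluster).
- a = 30%, b = 40%: kept 0.70 × 0.60 = 0.42, or 315 people (12.6 per cluster).
- Discarded although follow-up exists: from 0.05 × 0.60 = 3% (about 23 people) to 0.30 × 0.90 = 27% (about 203 people).

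**Power.** With 12 and 13 clusters, m analysed per cluster and DE = 1 + (m − 1) × 0.1, power = Φ(0.5/SE − 1.96), where SE² = DE/(12m) + DE/(13m).

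- m = 12.6: DE = 2.16, SE = 0.166, power 85.5%.
- m = 25.6: DE = 3.46, SE = 0.147, power 92.5%.
- Full 30: 93.4%.

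A t reference lowers these figures. For 12 against 12 clusters on 22 degrees of freedom it gives 79.9% at 12 per cluster and 90.1% at 30. Only the pessimistic corner then comes near 80%.

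**The step from 10 to 30.** With a full 30 in 12 clusters per arm, 80% power holds until 360/(1 + 29 × ICC) = 62.8, that is ICC = (360/62.8 − 1)/29 ≈ 0.16. A rise in the correlation from 0.10 to about 0.16 would use up the whole increase with no drop-out.

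**The case against.** The best defence is that the sentence concerns adherence, not data completeness. It ends by setting protocol fidelity aside, and the next sentence contrasts it with the per-protocol set. That narrows its purpose, but it still states who is included, and the model beside it cannot deliver that. Reading responder as someone who answered T0 does not help: the article uses the word for those recruited, and T0-only people would still fall out.

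A complete analysis plan is said to be published and is not shown. It may define the set or add missing-data sensitivity analyses, so the absence of these here is not criticised. It does not remove a conflict between rules that the article itself states.

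Several stronger readings are tempting and are not supported:

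- A reader might infer that the protocol expects up to two thirds of recruits to be missing. The larger recruitment is also meant to cover uncertainty in the effect and the correlation, and the calculation above shows that the correlation alone could absorb it.
- A reader might infer that dropping people without T0 biases the comparison between arms. T0 precedes randomisation, so failing to answer it cannot depend on allocation; the cost is mainly precision. Follow-up non-response can depend on arm, but the current model and the proposed one both rely on missing-at-random for it.
- A reader might infer that the baseline is regressed on itself. The article does not say that T0 rows are kept as outcomes.

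One objection shapes the remedy. Each questionnaire carries a consent form, so late entry is possible, and admitting people who join once allocation is known could introduce recruitment bias. The set must therefore be tied to recruitment before randomisation. Finally, no model recovers people without any score, so all 30 is unattainable as worded.

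**Conclusion.** The point holds as a conflict within one paragraph: the declared intention-to-treat set, the baseline covariate and the ban on imputation cannot all stand unless every recruit supplies T0 and at least one follow-up. This does not depend on any assumed rate. The size does, and the article gives none, so the 543 of 750 and the 42–86% are illustrations under independent missingness, not forecasts. Nor do they show that the stated power fails. The correction is worth making because it is nearly free and because the report would otherwise misdescribe its primary analysis set.

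**What to change.** Define the primary set as all professionals recruited before randomisation who have at least one adherence score, analysed in the arm of their cluster and regardless of protocol fidelity. Fix the list of recruits before allocation is released. Then choose one model:

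1. Enter T0, T1 and T2 as outcomes, with the baseline mean constrained to be equal across arms and the same cluster and subject random intercepts. The constraint is legitimate because T0 precedes randomisation, and the no-imputation sentence can stay.
2. Keep the baseline-covariate model, fill missing T0 with a mean or use a missing indicator, and amend the no-imputation sentence accordingly. T0-only people then still contribute nothing to the contrast, and the report should say so.

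Report by arm how many recruits supplied each pattern of T0, T1 and T2. The cost is a small change of model statement and wording, with no new data. The downside is reliance on missing-at-random, as in the current mixed model. That includes listed recruits who answer only after allocation is known.

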### Trial status

The trial commenced recruitment in April 2023. In June 2023, a total of 25 clusters (19 municipalities and 6 city districts) were recruited. In July, all 25 clusters had signed and returned the study agreements and were included in the trial. Data collection prior to randomisation started on August 7 and ended on August 31, 2023.

### Dissemination plans

Results will be published in peer-reviewed and scientific journals. We will present the results at national and international conferences and use it in education within health care services. Results will be disseminated regardless of the magnitude or direction of the effects.

## Discussion

This study will evaluate the effectiveness of a tailored implementation intervention to implement national recommendations on fall prevention among home-dwelling older adults in a municipal health care setting. In the intervention group, the fall prevention intervention will be locally tailored to each municipality and city district according to their needs and resources. The local tailoring and modifications to local settings are in accordance with international guidelines for fall prevention for older adults [4]. Moreover, matching departmental programs, such as national recommendations, and research has been recommended to ensure efficient resource allocation [55, 56]. To our knowledge, this is the first study in Norway evaluating health care services´ adherence to newly published national recommendations. It will provide valuable knowledge on implementing national recommendations within a complex municipality setting, and this knowledge can be further transferred to implementing recommendations within other areas of health care.

Fall prevention has been a part of clinical practice in the municipal health care in Norway for many years but is variably delivered. By including a broad spectrum of municipalities and city districts with different geography, demographics and priorities, we anticipate that we will gain knowledge on how to and to what extent fall prevention is delivered in different municipalities and city districts. By introducing a tailored implementation intervention with structure and practical guidance, we may help health professionals within the municipalities to increase their adherence to the national recommendations on fall prevention. We will also gain knowledge on the health professionals’ and managers’ experience of implementing evidence-based fall prevention in their municipalities and city districts and how municipalities can work to implement national recommendations. The study will provide knowledge which can inform the future development of municipal health care services for older adults at low, medium and high risk of falls.

The significant strengths of this study are the anchoring of the implementation intervention in implementation theory and evidence from systematic reviews on implementation interventions, the local tailoring and involvement of stakeholders through co-creation, and the demonstration of its feasibility. We will be able to provide knowledge from diverse clinical practices in Norway by including 25 municipalities and city districts in different regions, with the exception for the northern region. Given the potential contamination between intervention and control clusters, we will instruct the managers in the intervention municipalities to limit their sharing of documents and acquired knowledge.

We will report adherence to the national recommendations by use of self-reporting within a sample of health professionals representing their municipality. Notable considerations are that this questionnaire is self-reported and that it was developed and adapted within the project. The randomised design can help create a fair comparison across the intervention and control conditions. The lack of blinding might introduce a risk of bias. The participants in the intervention condition might be more motivated to report higher adherence than those in the control condition. To provide more data, and to be able to compare a potential impact on clinical outcomes, we will also examine injurious falls from health registers as secondary outcomes. Preferably, we would have included the fall rate in older adults as a measure; however, there are no data routinely collected on falls in the municipalities.

## Conclusion

This study will examine whether and how a comprehensive, tailored intervention, targeting municipal managers and health professionals, increases the implementation of national fall prevention recommendations in practice. It will also inform local strategies and implementation plans tailored to individual resources and teams in municipalities in Norway. Findings from this study will provide policy makers with knowledge on how national recommendations are implemented in the municipalities. Ultimately, we hope that it will substantially contribute to future reductions in falls amongst older adults.

## Data Availability

Economic and formative data collection materials are provided as additional files. Complete details on the operationalization of measures using electronic health data are outlined in the Statistical Analysis Plan (available from authors). The trial’s Data Safety and Monitoring Plan and protocol amendments are available from the first author.
